### Intervention

2.5

Patients will be submitted to transcutaneous electrical nerve stimulation of the posterior tibial nerve, based on the method described by Queralto et al (2006).^[27]^ This intervention will be supervised by a physiotherapist, who is a member of the research team with experience in this kind of therapy. A silicone auto adhesive electrode (positive electrode) will be applied approximately 3 to 4 cm above the tibial medial malleolus, and a second electrode (negative) will be placed just underneath the medial malleolus of the same leg. The electrodes will be linked to an electrical stimulation device (De Tens/Fes-2 channels, Neurodyn Portable Ibramed). The position of the electrode will be determined by visualization of rhythmic flexion of toes during stimulation. The intensity level will be determined based on the intensity immediately under the maximum sensitive threshold of the patient, usually between 10 and 25 mA. A 200-μs, 30-Hz current will be applied simultaneously in the 2 lower limbs, 30 minutes daily for 4 consecutive weeks, in the patient's home.

First, parents or guardians will be trained to perform PTNS on their children. Training sessions and supervised application will be provided until the parents feel confident enough to perform PTNS without supervision. From that point forward, PTNS will be performed daily in the household, as previously described. During the intervention period, patients should attend a supervised session of PTNS every 15 days, where the technique will be evaluated, and subsequent questions will be clarified. During this period, patients must maintain all therapeutic recommendations (drugs, diets, and behaviors) that had been previously prescribed by their referring physician. Any subsequent changes in treatment during the study period will not be avoided or delayed because of the study. Patients will be instructed to communicate with the research team about any changes in the therapeutic plan during the intervention period.

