**Figure 2 F2:**
[figure not shown]
Questionnaire addressing the evaluation of the applicability of the PTNS daily home sessions. PTNS = posterior tibial nerve stimulation.

Additionally, each patient will be monitored throughout a standardized week diary (stool frequency, stool consistency according to the mBSFS-c, frequency of fecal incontinence episodes, painful defecation, abdominal pain, blood in stools, laxative use and their doses, and adverse effects such as pain, nausea, vomiting, diarrhea, and flatulence). This diary must be filled out for 7 days, initiating 7 days before each of the assessment time points. Patients who use laxative medication will have the dosage quantity monitored, and any alterations will be registered as possible outcomes in the conclusion of the study, both in the case of increase or reduction of dosage.

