### Outcomes

2.9

Data analysis will be performed by focusing on the 3 assessment time points: assessment before the initiation of PTNS, immediately after the 4 weeks of intervention, and 4 weeks after the end of the intervention period. This analysis will be performed using the following clinical variables: number of defecations per week, number of episodes of fecal incontinence per week, need for diapers or underwear protection, need for medication for bowel habits, need for a special diet, straining and pain on defecation, presence of fecalomas, presence of abdominal pain, presence of bloody stools, need for enemas, and presence of perianal rashes or dermatitis. Also, we will analyze the results obtained by all the assessment instruments applied (mBSFS-C, BF-S, FCI questionnaire, AQLCAFI, and PEDsQL 4.0), to evaluate the outcomes of a functional status of bowel habits and the global quality of life.

As a secondary outcome, the applicability of PTNS will also be evaluated by the results of the specific questionnaire (Fig. 3), considering aspects that involve the practical difficulties for the application of this method and possible adverse events. All the situations that may be indirectly involved with the clinical results of PTNS, such as the increase or decrease of the laxative dose or any clinical or dietary changes, will also be analyzed as secondary endpoints.

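### Treatment changes are permitted during the study but analysed only as parallel outcomes, so the uncontrolled before/after comparison of defecations cannot separate them from stimulation

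*Protocol article*

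**What the plan says.** **Co-treatment (section 2.5).** The default is stability: "patients must maintain all therapeutic recommendations (drugs, diets, and behaviors) that had been previously prescribed by their referring physician". The text then leaves room for change: "Any subsequent changes in treatment during the study period will not be avoided or delayed because of the study". Changes are to be reported, but the instruction names one period only: "Patients will be instructed to communicate with the research team about any changes in the therapeutic plan during the intervention period".

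**Recording (section 2.8, text after Figure 2).** Laxative use and dose are entered in a diary kept for the 7 days before each of the three assessments. For patients on laxatives, "any alterations will be registered as possible outcomes in the conclusion of the study, both in the case of increase or reduction of dosage".

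**Role in the analysis (section 2.9).** The clinical variables compared across the time points begin with "number of defecations per week, number of episodes of fecal incontinence per week". They include the need for bowel medication and end with "need for enemas, and presence of perianal rashes or dermatitis". The next paragraph turns to circumstances that could bear on the clinical results of stimulation, "such as the increase or decrease of the laxative dose or any clinical or dietary changes, will also be analyzed as secondary endpoints".

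**Tests (section 2.10).** Time points are compared by paired t test and analysis of variance, or by Wilcoxon and Friedman tests. No test is described as adjusted for, stratified by or restricted on co-treatment.

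**Design and aim.** Section 2.1 describes one group followed over time. The Discussion states an intention to show efficacy in raising the number of spontaneous, complete movements. The variable in section 2.9 is the number of defecations, with no such restriction.

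**The concern.** Laxatives and enemas act directly on the variable that the sample size is built on. If a child's laxative dose rises between baseline and week 4, the extra stools enter that child's before/after difference in the same way as stools gained through stimulation. A control group would be exposed to the same changes in care and would allow them to be subtracted. Here nothing does that.

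The error can run either way. A child who manages on less laxative with the same stool count may have benefited, yet shows a difference of zero in the frequency comparison.

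Section 2.9 itself recognises that these changes may influence the results. Analysing them as separate endpoints shows how often they occurred, but not how much of the change in defecations goes with them. What is at stake is whether a significant paired test can be read as an effect of stimulation.

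**Working it through.** **1. The plan's own figure.** Section 2.3 gives a mean increase of 7 defecations per month, SD of changes 12, two-sided 5% level and power 0.85. For a paired test:

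n = [SD × (z₀.₉₇₅ + z₀.₈₅) / δ]² = [12 × (1.960 + 1.036) / 7]² = 26.4, rounded up to 27.

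With the exact noncentral t distribution, 29 are needed for 85%, and 28 give 84.5%. The stated 28 therefore reproduces and is not disputed. The steps below stay in its monthly unit.

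**2. What gain reaches significance.** With n = 28 and SD 12, the smallest mean change with p < 0.05 is t₀.₉₇₅,₂₇ × SD/√n = 2.052 × 12/√28 = 4.7 per month.

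**3. Shift from escalation alone.** The documents give neither the share of children escalated (f) nor the gain per escalated child (g). Both are assumptions. With no effect of stimulation, the mean change is f × g:

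| f | g | Shift per month | Share of the planned 7 |
|---|---|---|---|
| 20% | 7 | 0.20 × 7 = 1.4 | 20% |
| 20% | 16 | 0.20 × 16 = 3.2 | 46% |
| 30% | 7 | 0.30 × 7 = 2.1 | 30% |
| 30% | 16 | 0.30 × 16 = 4.8 | 69% |

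**4. Effect on the test.** Take SD 12 as the spread without escalation. Escalating only some children widens it to √[12² + f(1 − f)g²]. The chance of p < 0.05 with no stimulation effect is then:

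| f | g = 8 | g = 16 |
|---|---|---|
| 10% | 6% | 10% |
| 20% | 10% | 23% |
| 30% | 16% | 41% |
| 40% | 25% | 62% |

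The nominal rate is 5%. At f = 10% and g = 4 it stays at about 5%. A shift of 4.8 exceeds the 4.7 of step 2 but does not make significance certain: for f = 30% and g = 16 the SD becomes √(144 + 0.21 × 256) = 14.1, and the threshold rises to 2.052 × 14.1/√28 = 5.5.

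**5. Offset from reductions.** If a share r of children reduce laxatives and each loses the same g, the net shift is (f − r) × g. It is zero when r = f and negative when r > f. The tables above take r = 0.

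**The case against.** The strongest reply is that the plan already limits the problem. Section 2.5 makes unchanged therapy the default, and the permissive sentence only says that care will not be withheld because of the study. Section 2.6 discontinues patients whose bowel pattern worsens clinically, and they may be the ones most likely to be escalated. Both points stand as reasons why escalation may be uncommon. Neither settles the matter: changes remain allowed, a child can be escalated without worsening, and removing those who worsen introduces selection of its own. The contents of the eligibility table are not in the text at hand, so a stable-treatment criterion cannot be checked. Such a criterion would in any case govern entry, not later changes.

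A second reply is that linking treatment changes to the main comparison is commonly left to an analysis plan, which is not shown. That would answer mere silence. The article, however, gives these changes a role (outcomes and secondary endpoints) and names unadjusted tests for the comparison. It is fair to add that this role does not rule out a sensitivity analysis.

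Two stronger readings are tempting and should be set aside. A reader might infer that treatment changes appear only among the secondary endpoints. In fact the need for bowel medication and for enemas stands in the main list of variables in section 2.9, so both will be shown beside stool frequency. A reader might also infer that an escalated child is declared a success of stimulation, or that a child who reduces laxatives is recorded as unchanged. No success or responder rule exists, and dose reductions are registered as outcomes. The gap concerns the frequency comparison alone.

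**Conclusion.** The concern holds in a limited form. The article permits co-treatment changes, treats them as parallel outcomes, and compares all defecations before and after without reference to them and without a control arm. Gains from increased laxatives or enemas may therefore be credited to stimulation, and reductions may mask a benefit.

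The size is unknown. The shift of 1.4 to 4.8 per month against the planned 7 rests on assumed values (20 to 30% escalated, 7 to 16 defecations gained by each) and on no offset from reductions. A reader might take the false-positive rates as a forecast, but the documents do not support that. The 62% needs 40% of children escalated with a gain of 16 each and none reduced; with few or small changes the rate stays near 5%. The documents support saying that the comparison is open to this bias in either direction, not that the bias will occur or that it will favour stimulation.

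**What to change.** Leave clinical care exactly as it is, and keep the comparison of defecations regardless of treatment changes. Pre-specify beside it:

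- (a) the same comparison in children whose laxative dose, bowel drugs and enema use, as recorded in the diary week and the interview, are unchanged from baseline;
- (b) a conservative analysis in which a child with an increase in any of these counts as not improved, so that a positive change is set to zero and a negative one is kept.

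Report the number of children with increases and with reductions at each time point. Attribute a gain to stimulation only if the analyses agree, and say in advance what agreement means. Similar direction and size is a better standard than significance in the subset. Agreement is necessary for that attribution, but it does not remove the other limits of a before/after design.

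Analysis (b) belongs beside the main comparison and should not replace it. It is one-sided by construction and treats a trivial dose increase as complete failure.

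**Cost.** Analysis wording and a little more work. The diary and interviews supply most of the data. Changes between diary weeks after the intervention may not be fully captured, because the reporting instruction covers the intervention period only; the report should say so. Subset (a) is smaller and possibly selected. With 20 of 28 children left (30% excluded: 0.70 × 28 = 19.6), the 95% half-width at SD 12 goes from 4.7 to 2.093 × 12/√20 = 5.6 per month. The estimated effect may also be smaller.

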### Adherence to treatment and related adverse events

2.6

The research team members will register the treatment of patients in all the biweekly sessions of supervised PTNS and will investigate the possible occurrence of adverse events. At any point during the study, the patients/parents/guardians will be able to contact the research team by telephone to communicate possible adverse events and clarify any doubts. Patients who experience adverse effects or clinical worsening of the evacuatory pattern or who request will be discontinued from the study.

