In 2014, the European Society for Pediatric Gastroenterology, Hepatology, and Nutrition and the North American Society for Pediatric Gastroenterology, Hepatology, and Nutrition published a guideline that provides evidence-based recommendations for the evaluation, treatment, and follow-up of children with FC.^[3]^ The well-founded point for the treatment of FC consists of education of the child and parents, behavioral modifications, and laxative therapy.^[3,12]^ Therefore, conventional medical management of FC consists of pharmacological and nonpharmacological interventions. The pharmacological treatment of FC with laxatives involves 3 steps; disimpaction, maintenance treatment, and weaning. Nonpharmacological interventions involve education, demystification, explanation, guidance for toilet training, scheduled toilet sits, establishing a reward system, and keeping a defecation diary.^[3,13,14]^

In tertiary care centers, approximately 50% of children with FC managed with conventional treatment will be recover and taken off laxatives within 6 to 12 months, but the others, the symptoms can persist into adulthood despite intensive laxative treatment.^[15]^ Thus, a subset of patients may present with an unsatisfactory response and only minor improvement of symptoms. These children experience severe and long-lasting symptoms with recurrent fecal impactions, clinically characterized by extended intervals between defecation episodes, the passage of a large amount of stools once every 7 to 30 days and fecal incontinence that respond poorly to conventional therapy. Accordingly, when symptoms are irresponsive to optimal conventional treatment for at least 3 months, these children are considered to have intractable FC.^[3,16]^

Unfortunately, treatment options for children with constipation refractory to conventional treatment are limited. The most recent guidelines from the European and North American Pediatric Gastroenterology societies on the evaluation and treatment of FC in children recommend consideration of anal sphincter botulinum toxin injection, transanal irrigation, antegrade continence enemas, sacral nerve stimulation, and partial or total colonic resection for treatment of intractable constipation.^[3,10,17]^

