### Patient selection and recruitment

2.3

The estimated sample size is 28 patients, calculated for a paired *t* test (before and after intervention), based on an estimated mean increase of 7 defecations per month (according to data from previous PTNS studies^[25,26]^), an estimated standard deviation of changes = 12, a 2-tailed *α* = 0.05 and a test power *β* = 0.85. The sample will be comprised of children selected from the Pediatric Gastroenterology Outpatient and Pediatric Surgery Outpatient of the Clinics Hospital of the Botucatu Medical School -UNESP. The patients will be invited to attend an initial consultation to inform them about the study methods and apply the eligibility criteria.

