### Assessment interviews

2.8

In all assessment time points, patients and/or their guardians will participate in semi-structured interviews to determine the functional results of the intervention, concerning patient bowel habits and quality of life. These interviews will be conducted by the same member of the research team and will last approximately 40 minutes. The following assessment instruments will be applied: a questionnaire addressing the current clinical status (Fig. 1); the modified Bristol Stool Form Scale for children (mBSFS-C)^[28–30]^ to analyze the stool consistency (see mBSTS-C, Supplemental Digital Content 4); the bowel function score (BF-S)^[31]^ to evaluate the functional status of bowel habits (see BF-S, Supplemental Digital Content 5); the fecal continence index (FCI) questionnaire,^[32,33]^ based on the clinical evaluation of fecal continence (see FCI, Supplemental Digital Content 6); the assessment of quality of life in children and adolescents with fecal incontinence (AQLCAFI)^[32,33]^ (see AQLCAFI, Supplemental Digital Content 7) and the pediatric quality of life inventory version 4.0 (PEDsQL 4.0)^[34,35]^ to assess the quality of life (see PEDsQL 4.0, Supplemental Digital Content 8); and a questionnaire addressing the evaluation of the applicability of the PTNS daily home sessions (Fig. 2).

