### Statistical analysis

2.10

Statistical and descriptive analysis will be performed to characterize the patients before the intervention. Then, a comparative statistical analysis will be carried out involving the results obtained for the variables analyzed in the 3 assessment time points. Continuous numerical data will be expressed as the mean ± standard deviation and median (interquartile range). Proportions will be presented as percentages with their respective reliability intervals. The comparison between the assessment time points will be made using different statistical tests, according to variables analyzed and the normality distribution of data obtained by Shapiro–Wilk and Kolmogorov–Smirnov tests. Nominal variables will be analyzed using the McNemar test. Continuous numerical variables of parametric distribution will be analyzed using the *t* test for paired samples and the analysis of variance. Continuous numerical variables of nonparametric distribution and ordinal variables will be analyzed using the Wilcoxon and Friedman tests. The significance level will be established at 5%, and the analysis will be performed using SPSS 22.0 software for Windows.

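### Children whose bowel pattern worsens leave the study, not only the stimulation, so the one-group before/after comparison selectively loses poor outcomes; the size of the bias towards benefit cannot be derived from the protocol

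*Protocol article*

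**What the plan says.** The rule is in section 2.6 (Adherence to treatment and related adverse events): "Patients who experience adverse effects or clinical worsening of the evacuatory pattern or who request will be discontinued from the study". The object of the sentence is the study, not the stimulation.

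Four other parts of the article bear on it:

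- **Design (2.1).** Every child receives stimulation. No control group is described.
- **Outcomes (2.9).** The variables include "number of defecations per week, number of episodes of fecal incontinence per week", along with straining and pain, fecalomas, enemas and quality-of-life scores. The sample size (2.3) is "based on an estimated mean increase of 7 defecations per month".
- **Data collection (2.7, 2.8).** There are three assessments: before stimulation, at the end of the 4 weeks, and 4 weeks later. On the diary, section 2.8 says: "This diary must be filled out for 7 days, initiating 7 days before each of the assessment time points".
- **Analysis (2.10).** Time points are compared within patients. Normally distributed variables get the *t* "test for paired samples and the analysis of variance"; the others get Wilcoxon, Friedman or McNemar tests.

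On concurrent treatment, section 2.5 says: "Any subsequent changes in treatment during the study period will not be avoided or delayed because of the study".

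**The concern.** The trigger for removal overlaps the quantity being estimated. A child who does badly on bowel pattern is more likely to be taken out, and there is no comparison arm in which the same loss could offset it. The mean change among those who remain is then shifted towards benefit even if stimulation does nothing. The Discussion intends to read that change as efficacy.

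What is lost depends on when the child is removed:

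- **Before week 4**, for example at a supervised session during the intervention period: no post-treatment diary or interview exists.
- **At week 4**: the post-intervention value is kept and only the later follow-up is lost.

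Incontinence, pain and quality-of-life results face the same selection. The problem lies in data collection: an analysis plan could impute or score a removed child, but it could not supply the measurement.

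**Working it through.** **1. The plan's own figure.** Inputs from section 2.3: mean change 7 per month, SD of change 12, two-sided alpha 0.05, power 0.85.

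n = (12 × (1.960 + 1.036) / 7)² = 26.4. Adding the small-sample correction 1.960²/2 = 1.9 gives 28.3. Exact power of the paired t test at n = 28 is 0.845. The stated 28 reproduces.

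**2. Illustration of the bias, normal model.** From the protocol: n = 28 and SD 12. Assumed: no true effect; the k children with the worst interim course are removed (k = 1, 2, 3); the interim course correlates r = 0.3 to 0.7 with the final change.

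Expected shift = 12 × r × (mean of the top 28 − k standard normal order statistics out of 28). Those means are about 0.074, 0.138 and 0.197 for k = 1, 2, 3. For k = 3, r = 0.7: 12 × 0.7 × 0.197 = 1.65.

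The false-benefit rate is the chance of a significant increase in a two-sided 0.05 paired t test when nothing is going on. It is nominally 0.025. The rates come from 40,000 simulated trials per scenario.

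| Worst removed | Shift per month, r = 0.3 / 0.5 / 0.7 | False-benefit rate |
|---|---|---|
| 0 | 0 | about 0.025 |
| 1 | +0.27 / +0.45 / +0.62 | 0.03 to 0.05 |
| 2 | +0.50 / +0.83 / +1.16 | 0.04 to 0.08 |
| 3 | +0.71 / +1.18 / +1.65 | 0.05 to 0.12 |

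Against the planned 7, the shift is 0.27/7 = 4% to 1.65/7 = 24%.

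**3. Removals that do not lower counts.** A child may be removed for diarrhea, which takes out a high count. With the two lowest and the one highest removed, the shift falls to +0.23 (r = 0.3) to +0.51 (r = 0.7). A child may also worsen on pain or incontinence without a lower count.

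**4. Counts bounded at zero.** The Introduction describes intractable cases as "the passage of a large amount of stools once every 7 to 30 days", and such children have little room to fall. The follow-up count is taken as gamma with mean equal to baseline (no effect), with k = 3. The baselines and the SD of 6 are assumed.

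| SD | Baseline per month | Shift, r = 0.3 to 0.7 | False-benefit rate | Rate with no removal |
|---|---|---|---|---|
| 12 | 4 to 16 | +0.3 to +1.2 | 0.001 to 0.044 | 0.001 to 0.010 |
| 6 | 8 to 16 | +0.3 to +0.7 | 0.02 to 0.08 | 0.01 to 0.02 |

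At SD 12 the rate is below 0.025 in 6 of the 8 baseline-by-correlation combinations.

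**5. What follow-up would leave.** Children kept in follow-up may be on rescue treatment by then. If three of 28 gain g per month from it, the residual shift is g × 3/28:

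- g = 3.5 (assumed): 0.375, about +0.4. Normal-model rate about 0.04.
- g = 7 (assumed): +0.75. Normal-model rate 0.05 to 0.065.

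Compared with removing the three children, for g = 7:

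- Normal model: no gain at r = 0.3 (+0.75 against +0.71), a clear gain at r = 0.5 and 0.7.
- Bounded, SD 12: worse at r = 0.3 for every baseline (+0.75 against +0.31 to +0.61); better at r = 0.7 except at baseline 4 (+0.75 against +0.48).
- Bounded, SD 6: no better or worse in all six combinations (+0.75 against +0.31 to +0.74; rate 0.05 to 0.10 against 0.02 to 0.08).

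For g = 3.5, the residual of 0.375 is below the removal bias at every r in the normal model and in most bounded combinations.

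**The case against.** **The wording may be loose.** Sections 2.1 and 2.8 place all children at all three assessments, the flowchart and the supplementary checklist are not shown, and in a condensed article leaving the study may mean leaving the treatment course. This lowers confidence. But nothing shown extends the assessments past discontinuation, and if only stimulation was meant, the same edit corrects the sentence.

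**The size rests on assumptions.** This stands. Only n, the SD of 12 and the gain of 7 come from the protocol. The number removed, the correlations, the baselines, the SD of 6 and the rescue gains do not.

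**Keeping the children may not help the stool count.** This stands in part. With a large rescue gain, follow-up can leave as much bias as removal or more. It remains the better choice because the values, the reasons for stopping and the rescue treatment then become visible, whereas removal hides all three.

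**Part of this belongs in an analysis plan.** Missing-data methods do, and their absence here is not the complaint. Laxative doses and treatment changes are already recorded under sections 2.5, 2.8 and 2.9, though not expressly after discontinuation.

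**Scoring stopped children as failures.** A reader might propose coding these children as failures on the yes/no outcomes. Section 2.9 does not support that: it defines no success/failure endpoint, only separate items such as bloody stools or perianal rash. A child stopped for fewer stools would be given symptoms that nobody observed.

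**Conclusion.** The point holds and is worth correcting. Followed literally, section 2.6 removes children because of a poor course on the outcome, in a design with no control group and no data collection outside three assessments. The direction for worseners is towards benefit. Removal for adverse effects has no clear direction for stool frequency.

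The size is unknown and, as a judgement, probably modest if few children are removed: +0.3 to +1.7 per month in the normal illustration, less with counts bounded at zero.

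Two stronger readings are tempting and not supported:

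- **That the rule makes a false efficacy claim likely.** Much larger shifts do arise if it is applied very strictly: +1.7 to +3.4 if every child with at least 12 fewer defecations per month is removed, and +9.6 if every child with any decline is. The article gives neither a definition nor a rate of worsening that would point to such removal, and a child first found worse at week 4 still contributes that value.
- **That continued follow-up brings the bias to zero.** That would hold only if rescue had no effect on the counts, and section 2.5 lets treatment change freely.

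**What to change.** Leave the clinical decision to stop as it is. In section 2.6, make stimulation, rather than the study, the thing from which the child is discontinued, and add:

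> Children who stop stimulation still complete the scheduled post-intervention and 4-week interviews and diaries unless consent is withdrawn. Any laxative, enema or other rescue treatment started or increased after stopping is recorded. All children who started stimulation are analysed.

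Report the number stopped, by reason, and the number given rescue treatment beside the before/after result, and read the change together with those counts.

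**Cost.** The text change is a few sentences, but section 2.11 sends amendments to the ethics committee and the Discussion says recruitment is under way, so signed consent may need revisiting. A child stopped before week 4 takes at most two interviews, each of which "will last approximately 40 minutes", and two 7-day diaries. For three such children that is 6 × 40 minutes = 4 hours and 6 diaries, all of it already scheduled. The mean change may come out less favourable, and some stool-count bias may remain because of rescue.
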